# Screening, Recruitment and Consent

Screening, recruitment and consent procedures will be required for midwives receiving the research intervention, and midwives and pregnant women providing quantitative and qualitative outcome and process evaluation data.

11.1 Identification and screening of midwife research participants

- Potential midwife participants will be identified through staff lists at the participating sites by the local PIs/research midwives who have access to staff data.
- An eligibility screening form will be completed by the local PIs/research midwives to document participants’ fulfilment of the entry criteria for all midwives considered for the study and subsequently included or excluded.

11.2 Recruitment procedures for midwife research participants

- All potential participants eligible to receive the intervention (training) will be invited to participate and the study explained to them by the local PIs/research midwives within the intervention arm NHS Trusts. A study Participant Information Sheet (PIS) for participating in the intervention will be provided at this time and the midwife will be allowed to take this away for consideration.
- We aim to recruit 15 midwives in each participating NHS Trust to provide quantitative outcome data. To allow for withdrawal and loss to follow up, a random selection of 18 midwives in each site will be invited to provide quantitative data for the study (including baseline data, outcome measures, and quantitative process evaluation measures) and the study explained to them by the local PIs/research midwives within the NHS Trusts. A study PIS for collecting outcome data will be provided at this time and the midwife will be allowed to take this away for consideration.
- We aim to recruit a further 5 midwives from each NHS Trust to provide qualitative process evaluation data. To allow for withdrawal and loss to follow up, a random selection of 7 midwives in each site will be invited to participate in qualitative focus groups and the study explained to them by the local PIs/research midwives within the NHS Trusts. Random sampling has been chosen for this element of qualitative research as an attempt to avoid engaging with only those midwives with a specific interest in the topic, as the process evaluation requires the exploration of positive and negative perspectives. A study PIS for focus groups will be provided at this time and the midwife will be allowed to take this away for consideration.
- A screening log will be kept by the local PIs/research midwives in each site to:
  - Document details of midwives invited to participate in the intervention, to provide quantitative data, and to provide qualitative focus group data.
  - Document reasons for non-participation among midwives who decline participation of any stage if they are happy to provide this information.
  - Ensure potential participants are only approached once for each aspect of recruitment (i.e. the same midwives will only be approached once to receive the intervention, and among those who agree midwives will only be approached once to provide quantitative or qualitative data).
- Recruitment to provide the quantitative baseline (and follow up) data will be carried out prior to randomisation of clusters into intervention or control arms. Midwife participants to be recruited to receive the intervention, and for qualitative focus groups, will only be required in the intervention arm. Therefore the recruitment for these stages will take place following randomisation of clusters.
- Midwives will be reimbursed any travel expenses incurred relating to recruitment, participating in the intervention, and data collection.

11.3 Consent procedures for midwife research participants

- Informed consent discussions will be untaken by a member of the research team (as per delegation log) involved in the study, with opportunity for midwives to ask any questions.
- Following receipt of information about the study, midwives will be given reasonable time to decide whether or not they would like to participate.
- Those wishing to take part will provide written informed consent by signing and dating the relevant study consent form which will be witnessed and dated by a member of the research team with documented, delegated responsibility to do so.
- Written informed consent will be obtained prior to any study specific procedures/investigations.
- The original signed consent form will be retained in the Investigator Site File, and a copy provided to the midwife participant.
- The right to refuse to participate without giving reasons will be respected.
- 1^st^ consent: Consent will be taken from the midwives randomised to provide quantitative outcome measures prior to baseline data collection, and prior to intervention delivery.
  - Due to the geographical location of some community midwife bases, face-to-face consent is not practical. An alternative option for the midwives questionnaire-based data collection is for the PIS and questionnaires to be posted to community midwives. The community midwives have the option of discussing the research over the phone with a member of the research team, and completion and return of the questionnaire is implied consent.
- 2^nd^ consent: Consent will be taken from all the midwives in the intervention arm to receive the intervention prior to attending the intervention.
- 3^rd^ consent: Consent will be taken from midwives recruited to participate in focus groups following receipt of the intervention.

11.4 Identification and screening of women to provide outcome and process data

- Screening for eligible pregnant women participants will use the antenatal booking data recorded on the participating sites electronic patient records for the recruitment time period to assess eligibility of women attending their 12 week scan appointment. Screening will be carried out by the local PIs/research midwives who have access to this data at their local site.
- An eligibility screening form will be completed by the local PIs/research midwives to document participants’ fulfilment of the entry criteria for all women considered for the study and subsequently included or excluded.

11.5 Recruitment procedures for women to provide outcome and process data

- Baseline data: We aim to recruit 15 pregnant women in each NHS Trust to provide quantitative baseline data. To allow for withdrawal and loss to follow up, a random sample of 18 eligible women attending the NHS Trust for their 20 week scan at each site will be invited to provide quantitative questionnaire data at baseline, prior to the intervention delivery in order to identify the similarity of outcome measures within and between sites prior to the intervention. Recruitment will be carried out by the local PIs/research midwives and the study will be explained to potential participants. A study PIS for one-off collection of baseline data at 20 weeks gestation will be provided at this time and the women will be allowed to take this away for consideration. Recruitment for women providing baseline data will be carried out prior to randomisation of clusters into intervention or control arms.
- Outcome data: We aim to recruit 15 pregnant women in each NHS Trust to provide quantitative outcome data. To allow for withdrawal and loss to follow up, women at each site will be approached and invited to provide quantitative post-intervention outcome data (questionnaire-based data following their 12 week scan; weight measurements and questionnaire-based data in the 3^rd^ trimester; and repeat measures postnatally) until 30 women per site have consented and returned their first questionnaire. The study will be explained to all women approached by the local PIs/research midwives. A study PIS will be provided at this time and the women will be allowed to take this away for consideration.
- Qualitative data: we aim to recruit and interview 5 pregnant women from each NHS Trust to provide qualitative process evaluation data (semi-structured interviews) in their 3^rd^ trimester and again at 3 months postnatal. To allow for withdrawal and loss to follow up, the opportunity to participate in this qualitative research will be discussed with all women consenting to provide quantitative outcome data until 10 eligible women at each site have consented. A study PIS will be provided at this time and the women will be allowed to take this away for consideration.
- As a recruitment and retention incentive due to the potential burden of data collection without any direct benefit of participation in the study, women will receive a £10 high street gift voucher for every data collection time point (maximum of £10 for women who provide only baseline quantitative data, £60 for women who provide quantitative outcome data at all time-points, and £80 for women who provide quantitative outcome data plus qualitative interview data at both time-points). Women will also be reimbursed any travel expenses incurred relating to recruitment and data collection.
- The random sampling and recruitment procedures will continue until the target sample sizes are reached.
- A screening log will be kept by the local PIs/research midwives in each site to:
  - Document details of women invited to provide quantitative outcome data
  - Document details of women invited to provide qualitative interview data
  - Document reasons for non-participation among women who decline participation of any stage if they are happy to provide this information.
  - Ensure potential participants are only approached once for each aspect of recruitment (i.e. the same women will only be approached once to provide quantitative outcome data and to provide qualitative interview data).

11.6 Consent procedures for women to provide outcome and process data

- Informed consent discussions will be untaken by a member of the research team (as per delegation log) involved in the study, with opportunity for women to ask any questions.
- Following receipt of information about the study, women will be given reasonable time to decide whether or not they would like to participate.
- Those wishing to take part will provide written informed consent by signing and dating the relevant study consent form which will be witnessed and dated by a member of the research team with documented, delegated responsibility to do so.
- Written informed consent will be obtained prior to any data collection.
- The original signed consent form will be retained in the Investigator Site File, a copy will be filed in the women’s antenatal notes, and a copy provided to the participant.
- The right to refuse to participate without giving reasons will be respected.

# Study Intervention Details

The details of the intervention are reported using the template for intervention description and replication (TIDieR) checklist and guide [[52](#_ENREF_52)].

**Brief name:** GLOWING Pilot Cluster RCT

**Why:** The background to, and theoretical basis of, the intervention are described in section 7. The aim of the intervention and specific objectives of the pilot study are detailed in section 8.

**What: Materials and Procedures**

Materials – intervention arm only: All teaching materials will be provided to the midwives participating in the intervention in a training pack, as well as being available via a study website. Midwives will also be provided with one hard copy each of the First Steps Nutrition Trust charity resource “Eating well for pregnancy: A practical guide” (<http://www.firststepsnutrition.org/newpages/Pregnancy/pregnancy_practical_guide_for_healthy_pregnancy.html> [last accessed 23/11/2015]).

The NHS Trusts in the intervention arm will also be provided with resource packs to share with pregnant women with obesity throughout the duration of the pilot study. The resources to be included in this pack comprise of existing credible information resources on maternal obesity and weight management in pregnancy from charities and Start4Life. An additional leaflet is being developed for this study to identify local support for women with pregnancy and postnatal nutrition and physical activity (e.g. local aqua natal classes), as well as listing further credible information sources (e.g. NHS Choices, Start4Life).

- Tommy’s the Baby Charity:
  - Booklet: Managing your weight in pregnancy <https://www.tommys.org/sslpage.aspx?pid=602&nccsm=21&__nccspID=967> [last accessed 23/11/2015]
  - Leaflet: Your guide to staying active in pregnancy <http://www.tommys.org/file/Exercise.pdf> [last accessed 23/11/2015]
- Leaflet from First Steps Nutrition Trust identifying resources available for women to purchase (hard copies) or download for free, including:
  - Pregnancy: Eating well for pregnancy: A practical guide; <http://www.firststepsnutrition.org/newpages/Infants/infant_feeding.html> [last accessed 23/11/2015]
  - Postnatal: Eating well for New Mums: Including information for breastfeeding mothers; Eating well: the first year; Eating Well Recipe Book; Breastmilk and breastfeeding: a simple guide; and Infant milks: a simple guide to infant formula, follow on formula, and other infant milks <http://www.firststepsnutrition.org/newpages/Infants/infant_feeding.html> [last accessed 23/11/2015]
- Start4Life
  - Booklet: healthy habits for baby and you <https://campaignstorage.blob.core.windows.net/start4life/development/uploads/ckeditor/attachments/9/Start4Life-Healthy_Habits.pdf> [last accessed 23/11/2015]

# Randomisation

13.1 Intervention randomisation

Computer randomisation of the four pilot clusters (NHS Trusts) into intervention or control arms will be will be stratified by size of maternity service within the NHS trust (based on number of bookings/year in each NHS Trust: large units – Newcastle and Northumbria NHS Trusts; small units - Gateshead and South Tyneside). Randomisation will be performed by a statistician using anonymised unique IDs for each trust to prevent allocation bias (e.g. Large1, Large2; Small1, Small2). Midwives will be consented to take part and baseline data will be collected before randomisation (i.e. allocation concealment prior to consent and baseline data collection).

13.2 Randomisation for data collection

The midwives and women (baseline only) invited to provide quantitative and qualitative data for the pilot study will be randomly selected within each cluster. Local PIs/research midwives with access to staff lists and electronic medical records at each site will allocate a unique anonymised ID number to each eligible participant (midwife and women). Random selection of midwives and women at each site will be carried out by a statistician using the list of anonymised unique IDs. For the follow up post-intervention data collection from pregnant women, a convenience sample will be used rather than randomisation. The ultrasound scan clinic appointment lists will be accessed by the research midwives in each site, and the women’s electronic records will be screened against the inclusion criteria to identify eligible women to approach for consent.

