  - Total number of participants eligible for the intervention for each site (data collection by local PIs/research midwives at each trust)
  - Total number of participants who attend the intervention at each site (log to be maintained by the midwife facilitator for each intervention delivery session, to include number of participants in attendance at each session)
  - Location of intervention delivery for each session (log to be maintained by the midwife facilitator for each intervention delivery session, to include location)
  - Number of intervention sessions delivered (log to be maintained by the midwife facilitator for each intervention delivery session, each session to be numbered with unique ID)
  - Dates and times of each intervention session at each site (log to be maintained by the midwife facilitator for each intervention delivery session, to include date of session)

b) Piloting data collection procedures will include recruitment and retention of participants completing outcome measures, and data yield.

- Recruitment and retention: data will be collected on eligibility and consent rates, and retention of participants providing outcome measures at the scheduled time points. Recruitment and retention data will be collected at the levels of NHS Trust, midwives, and women. Data will be analysed to identify any systematic differences between those who agree to participate in the study and the general maternity population in the NHS Trusts recruited and thereby ascertain the extent of any participation bias. Data collection will include:
  - Number of midwives eligible to be approached to provide quantitative or qualitative data (data to be collected by the by local PIs/research midwives during recruitment process)
  - Number of pregnant women eligible to be approached to provide quantitative baseline data (data to be collected by the by local PIs/research midwives during recruitment process)
  - Number of pregnant women eligible to be approached to provide quantitative outcome data and qualitative process evaluation data (data to be collected by the by local PIs/research midwives during recruitment process)
  - Numbers of NHS Trusts, midwives and women approached/accepted/declined to participate in the study (data to be collected by the by local PIs/research midwives during recruitment process)
  - Number of NHS Trusts retained until the end of the study (log of recruitment and retention to be maintained by the CI)

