# Study Data

In addition to the data required to meet the aims of the pilot study (detailed in section 9), one of the purposes of the pilot study is to determine which outcome to use as the primary outcome and which should be secondary in a definitive trial. The proposed primary and secondary outcomes will be collected during the pilot study in line with the primary and secondary aims of the intervention.

- Primary aim: midwives behaviours
- Primary outcome: change in midwives clinical practice
- Potential primary outcome measures:
  - Midwives self-reported practice
  - Women’s self-report of their midwives practice
  - Case note audit of recorded midwifery practice
  - Vignettes of different types of consultation (simulated practice)
- Secondary aim: women’s weight and weight-related behaviours
- Primary outcome: change in weight from booking
- Potential primary outcome measures:
  - Pregnancy weight: 3^rd^ trimester,
  - Postnatal weight: 3, 6, 9, 12 months
- Secondary outcomes: 3^rd^ trimester and 3, 6, 9, 12 months postnatal
  - Dietary behaviours
  - Physical activity behaviours
  - Psychosocial measures for weight-related behaviours
  - Therapeutic alliance with midwives (3^rd^ trimester of pregnancy only)
  - Quality of life

All primary data collection will be anonymised using the participant’s unique study ID number. An overview of the study data are presented in table 2.

Table 2. Data collection type, populations, sites, time points, and consent

|  | **Baseline (pre-intervention)** | **Intervention delivery** | **1 month post intervention** | **3 months following intervention delivery (to all midwives)** | **6 months following intervention delivery (to all midwives)** | **3 months postnatal** | **6 months postnatal** | **9 months postnatal** | **12 months postnatal** |
| --- | --- | --- | --- | --- | --- | --- | --- | --- | --- |
| **Maternity electronic patient records (all clusters)** | Eligible pregnant women’s characteristics |  |  |  |  |  |  |  |  |
| **Random sample of 18 women attending 20 week scan/ cluster (all clusters)** | Consent, women's characteristics, questionnaire data.  Case note audit (economic evaluation phase 1) |  |  |  |  |  |  |  |  |
| **Random sample of 18 midwives/ cluster (all clusters)** | Consent, midwives characteristics, questionnaire data |  |  | Questionnaire data | Questionnaire data |  |  |  |  |

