| **All community midwives/cluster (intervention arm, 2 clusters)** |  | Consent, intervention delivery, completion of evaluation forms |  |  |  |  |  |  |  |
| **Random sample of 7 midwives/ cluster (intervention arm, 2 clusters)** |  |  | Consent, focus groups |  |  |  |  |  |  |
| **Convenience sample of 30 women/ cluster (all clusters)** |  |  |  |  | Consent women at 12 week scan and questionnaire data; follow up at 36 weeks, questionnaire data and weight measurement | Questionnaire data, weight measurement, case note audit | Questionnaire data, weight measurement | Questionnaire data, weight measurement | Questionnaire data, weight measurement |
| **Convenience sample of 10 recruited women/cluster (all clusters)** |  |  |  |  | Consent at 12 weeks, semi-structured interviews (3rd trimester) |  | Semi-structured interviews |  |  |

Study data collection details:

- Maternity electronic patient records: pregnant women’s characteristics including maternal age, BMI, ethnic group, parity, employment status, socio-economic status (determined by postcode anonymised by data linkage with index of multiple derivation data) will be retrieved from the electronic patient records for all eligible women in their 3^rd^ trimester during the recruitment period. Data will be anonymised and aggregated to compare with recruited women to determine any participation bias for each site.
- Women at 20 week scan – baseline only: eligible women will be approached and consented by a member of the research team (as per delegation log) before the intervention delivery to provide baseline data on their characteristics (including maternal age, gestation, BMI, ethnic group, parity, employment status, qualifications, postcode), questionnaire data. This is a one off data collection to compare how similar women are within and between sites before the midwives caring for them have received any intervention. The questionnaire data are:
  - Self-report of their midwives practice specific to the guideline recommendations (developed to reflect the midwives self-reported routine practice behaviour measurements)
  - Dietary Quality Score (DQS – validated in non-pregnancy with additional pregnancy and postnatal specific questions included)
  - Pregnancy Physical Activity Questionnaire (PPAQ – validated in pregnancy)
  - Psychosocial measures for understanding weight-related behaviours in pregnant women questionnaire (validated in pregnancy)

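### Women giving outcome data are a post-allocation convenience sample with no stated order of approach, and the participation-bias comparison is specified on a different group of women

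*Protocol*

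**What the plan says.** **Sampling.** Midwives and baseline women are picked at random by a statistician from anonymised lists (13.2), and for the baseline women 11.5 adds: "Recruitment for women providing baseline data will be carried out prior to randomisation of clusters into intervention or control arms". The women who supply outcome data are handled differently: "For the follow up post-intervention data collection from pregnant women, a convenience sample will be used rather than randomisation".

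**Who recruits them.** Section 13.2: "The ultrasound scan clinic appointment lists will be accessed by the research midwives in each site". Section 11.5: "The study will be explained to all women approached by the local PIs/research midwives". Recruitment runs until each site has 30 women who have agreed and sent back a first questionnaire. No order of approach is given. A later bullet in 11.5 still speaks of random sampling continuing until targets are met, without limiting this to the baseline sample.

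**Who knows the arm.** Under 11.2, the midwives eligible for training are invited and the "study explained to them by the local PIs/research midwives within the intervention arm NHS Trusts"; this happens after the clusters are randomised. Section 14 lists partial blinding for the statistician, for the women, and for midwives at consent and baseline. It lists none for the staff who recruit women.

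**The check.** Section 9.1.1 b) sets out to compare participants with the wider maternity population and "thereby ascertain the extent of any participation bias". It describes pooled data from the period of recruitment and names no trimester. Study Data specifies instead that characteristics are retrieved "for all eligible women in their 3^rd^ trimester during the recruitment period". In Table 2, the row beginning "Maternity electronic patient records (all clusters" has one filled cell, under the pre-intervention baseline column.

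**The concern.** In a cluster trial the individuals who supply outcomes are often enrolled after the clusters are allocated. If the recruiters know the arm and have latitude over whom to approach, the women enrolled can differ between arms for reasons unrelated to the intervention. The consent rate, which is a pilot result in its own right, also comes to depend on an undocumented order of approach.

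The usual protection is to compare recruits with everyone who could have been recruited. That works only if the comparison group is the pool from which the recruits came. Here the text most specific about that group names women at a stage of pregnancy when nobody is recruited, and the schedule places the pull before the outcome women are recruited.

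At stake are the participation-bias result under objective 1 and the inputs taken forward to the definitive trial. Women's report of their midwives' practice is a candidate primary outcome there, and section 16.1 uses the pilot data for variability, proportions and the ICC.

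**Working it through.** **1. The plan's own numbers.** Section 16.2 aims for 15 women with outcome data per cluster and two clusters per arm: 15 × 2 = 30 per arm, as stated, and 15 × 4 = 60 in all. Recruitment of 30 per cluster gives 30 × 4 = 120 women. All 120 enter by convenience sampling.

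**2. Timing against allocation.**

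| Group | Selection | Relative to randomisation |
|---|---|---|
| Midwives giving questionnaire data | random | before |
| Baseline women (20 week scan) | random | before |
| Outcome women (12 week scan) | convenience | after; Table 2 puts their consent in a post-intervention column |

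The only one of these groups recruited after allocation is also the only one not chosen at random.

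**3. Do recruiters know the arm?** No sentence says so. The inference has three parts: the same category of site staff invites midwives to training in intervention Trusts only; this takes place after randomisation; and section 14 lists no blinding for them. It is a firm inference, but still an inference.

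**4. The comparison group.** The protocol does not define the third trimester, so I assume weeks 28 to 40. Appendix 4 places collection of women's reports about six months (26 weeks) after training starts.

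| Reading | Offset from outcome recruits (week 12) | Date of the pull |
|---|---|---|
| 9.1.1 b) alone | none necessarily | same window as recruitment |
| Study Data alone | 28 − 12 = 16 to 40 − 12 = 28 weeks | same window, later in pregnancy |
| Study Data with Table 2 | as above | about 26 weeks or more before outcome recruitment |

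On the third reading, the comparison women passed week 12 at least 16 weeks before the pull. Their 12 week scans therefore precede those of the outcome recruits by at least about 16 + 26 = 42 weeks. For the baseline sample the pull is contemporaneous, and the offset is 28 − 20 = 8 to 40 − 20 = 20 weeks.

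The mismatch does not depend on the exact start of the trimester. For any start after week 20, no woman attending either scan is in the comparison group on that date. If the recruitment window exceeded 16 weeks, the earliest recruits could reach the third trimester before it closed, so some overlap is possible on the second reading. A third-trimester group also leaves out pregnancies lost after the 12 week scan.

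**5. What the other records show.** Eligibility forms (11.4), the screening log with reasons for declining (11.5) and the counts of women eligible, approached, accepting and declining (9.1.1 b) give numbers and reasons. As described, they do not set the characteristics of recruits beside those of eligible women. That is the task of the record pull.

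**The case against.** Several stronger readings are tempting, and the document does not support them.

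- *That the record comparison is the only safeguard.* It is not. Forms, a log and counts are kept, and women are not told the arm.
- *That staff are said to choose among eligible women.* Section 13.2 says only that records are screened to find eligible women to approach. A convenience sample leaves room for discretion but does not state it. Staff might well approach everyone in turn.
- *That participation bias cannot be assessed at all.* Section 9.1.1 b) read alone permits a contemporaneous, correctly drawn pool. The pre-intervention timing rests on one cell of an overview table.
- *That a given amount of bias follows.* The document offers no figure for the strength of selection. An illustration built on motivation would be beside the point, because motivation is not among the recorded characteristics and a corrected pull would not reveal it.

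Two further points carry weight. Most characteristics compared (age, booking BMI, ethnic group, parity, deprivation) change little over a few months, so the offset may distort them only slightly. And this is a descriptive pilot with no between-arm test planned, women are a secondary population, and the SD for continuous outcomes comes from the control group, so a difference between arms does not enter it directly.

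These points limit the consequence. They do not reconcile the passages. When the comparison group is not the source population, a difference between recruits and comparators mixes participation with change over time and loss of pregnancies. Unrepresentative recruits within the control arm would still affect the SD.

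**Conclusion.** The point holds as a design weakness together with an internal inconsistency, worth correcting but modest in consequence. All 120 planned outcome women are a convenience sample recruited after allocation, with no fixed order of approach, by staff who very probably know the arm.

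Followed as Study Data and Table 2 are written, the participation-bias comparison uses women at least 16 weeks beyond the outcome recruits and 8 beyond the baseline recruits. It also predates outcome recruitment by about six months, so the sample most open to selection has the poorest match. These gaps rest on the assumed week 28 start and on the approximate training period in Appendix 4. Section 9.1.1 b) points to a better comparison, so the passages need reconciling.

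How far the recruits will in fact differ between arms, or from eligible women, cannot be derived from the protocol.

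**What to change.** - **Section 13.2:** state that all eligible women on the 12 week scan lists are approached consecutively until the target is reached. In 11.5, limit the reference to random sampling to the baseline women.
- **Study Data, Table 2 and 9.1.1 b):** use one definition throughout. Draw aggregate characteristics of all eligible 12 week scan attenders in each Trust's outcome recruitment window, and of eligible 20 week scan attenders in the baseline window. Add the second pull to Table 2.
- **Reporting:** compare recruited with eligible women by site and by arm.

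The cost is wording in these places, a different filter on a query already planned, one additional pull, and slightly less flexibility for clinic staff. Scan lists are already being screened, so consecutive approach adds little work.

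The change has limits that the report should state. It does not stop staff who know the arm from influencing consent, and it does not detect differences in traits that the records do not hold, such as motivation.
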